## Abstract

**Introduction:**

Children with congenital hemiplegia often present with limitations in using their impaired upper limb which impacts on independence in activities of daily living, societal participation and quality of life. Traditional therapy has adopted a bimanual training approach (BIM) and more recently, modified constraint induced movement therapy (mCIMT) has emerged as a promising unimanual approach. Evidence of enhanced neuroplasticity following mCIMT suggests that the sequential application of mCIMT followed by bimanual training may optimise outcomes (Hybrid CIMT). It remains unclear whether more intensely delivered group based interventions (hCIMT) are superior to distributed models of individualised therapy. This study aims to determine the optimal density of upper limb training for children with congenital hemiplegia.

**Methods and analyses:**

A total of 50 children (25 in each group) with congenital hemiplegia will be recruited to participate in this randomized comparison trial. Children will be matched in pairs at baseline and randomly allocated to receive an intensive block group hybrid model of combined mCIMT followed by intensive bimanual training delivered in a day camp model (COMBiT; total dose 45 hours direct, 10 hours of indirect therapy), or a distributed model of standard occupational therapy and physiotherapy care (SC) over 12 weeks (total 45 hours direct and indirect therapy). Outcomes will be assessed at 13 weeks after commencement, and retention of effects tested at 26 weeks. The primary outcomes will be bimanual coordination and unimanual upper-limb capacity. Secondary outcomes will be participation and quality of life. Advanced brain imaging will assess neurovascular changes in response to treatment. Analysis will follow standard principles for RCTs, using two-group comparisons on all participants on an intention-to-treat basis. Comparisons will be between treatment groups using generalized linear models.

**Trial registration:**

ACTRN12613000181707

## Background

Congenital hemiplegia occurs in over one million children under 21 years of age in the industrialised world and is the most common type of cerebral palsy (CP), accounting for 36% diagnosed with this lifelong condition [1,2]. These children have limitations in their capacity to use their impaired upper limb and bimanual coordination deficits which impacts upon daily activities and participation in home, school and community life [3]. There are currently two diverse intensive therapy approaches aimed at improving upper limb performance. Traditional therapy has adopted a bimanual training approach (BIM) and more recently, constraint induced movement therapy (CIMT) has emerged as a promising unimanual approach.

Our 2009 published meta-analysis evaluating the efficacy of all non-surgical approaches to upper limb rehabilitation highlighted the absence of strong evidence for any particular model of therapy for improving upper limb outcomes in congenital hemiplegia [4]. There was consistent evidence for a small supplementary benefit for use of intramuscular Botulinum Toxin A (BoNT-A) injections combined with various models of upper limb training. No particular model of training, whether it was Neurodevelopmental Therapy (NDT), CIMT or Intensive Hand Arm Bimanual Training (HABIT) demonstrated a superior effect on activity limitations [4]. In the last three years, a significant number of additional randomised controlled trials, particularly of CIMT have been published [[name], [name], [name]: Efficacy of upper limb interventions for children with unilateral cerebral palsy: systematic review and meta-analysis update**,** submitted].

Classic CIMT involves application of a full arm cast to the unimpaired upper limb which is worn for 21 consecutive days and accompanied by six hours daily of upper limb training (total dose 126 hours) [5]. This model of therapy, initially used with adults post stroke, demonstrated significant improvements in upper limb function that were retained at 12 months post intervention [6]. The classic CIMT model has been used in a small number of studies for children with congenital hemiplegia demonstrating improved quality and amount of use of the impaired upper limb and acquisition of new upper limb motor skills [5,7]. A subsequent study compared the full classic CIMT protocol to half dose (60 hours) and demonstrated that for three to six year old children with congenital hemiplegia, 63 hours of training was sufficient to drive changes in upper limb function [5,8].

Classic CIMT has been criticised for not being child friendly or clinically feasible to implement. A significant number of modified CIMT (mCIMT) models have been developed. These have varied from intensive group based interventions [9-12], intensive individual therapy [13,14], distributed group or individual intervention [16-21] delivered either in the clinic [9,10], community [11], or in the home [14,15,17,20,21]. Despite the different modes of delivery and environmental context, findings consistently demonstrate mCIMT is superior to standard or usual care of a lesser dosage to improve quality and amount of use of the impaired upper limb [17,21], bimanual and unimanual efficiency of movement [17,21] and bimanual performance [16].

In contrast, when mCIMT has been compared to an equivalent dose of intensive bimanual training or goal directed occupational therapy, minimal differences have been found on most clinical measures, as both interventions yield similar improvements [10,11,13]. This highlights that the dose of therapy may be the critical ingredient rather than the type of therapy (e.g. unimanual versus bimanual).

Constraint induced movement therapy and modified protocols have a significant limitation, that is, they do not allow practice of bimanual tasks. Goals identified by children and their caregivers tend to be bimanual in nature [11,19]. This has led to the development of hybrid models of therapy that combine mCIMT and bimanual training. Two studies have investigated differing hybrid models of mCIMT followed by bimanual training. A long duration, distributed model of therapy performed over an eight week period (six weeks mCIMT 54 hours; two weeks bimanual 18 hrs) found significant gains in unimanual, bimanual and individualised outcomes compared to standard care for 2.5 to eight year old children with congenital hemiplegia [22]. A short duration model delivered over a three week period (two weeks mCIMT 30 hrs, one week bimanual 2.25 hrs), however was not superior to usual care to improve movement efficiency but did yield significant changes in self-care [23].

The differences in findings may reflect variations in dosage, the choice of outcome measures, and intensity or density of training. Recent classic CIMT studies have also acknowledged the need for bimanual training to follow CIMT and have developed a “transfer package” to address this requirement [7,24]. Further support for the idea of sequential application of interventions was obtained from examination of neuroplasticity findings with Transcranial Magnetic Stimulation (TMS). Children receiving mCIMT had greater and earlier use-dependent neuroplasticity than those receiving BIM (in a masked comparison) immediately post intervention which was sustained at six months [25]. This has important implications for the timing of interventions and the potential for optimizing the strengths of both by sequential application.

There is currently little evidence to support traditional standard care block models of upper limb therapy (e.g. six to eight weekly one hour sessions), as these alone are unlikely to provide an adequate dose to drive changes in upper limb function. Occupational therapy home programs have been shown to be effective in a high quality randomised controlled trial [26] and could allow an adequate dose of therapy to be achieved if accompanied with a distributed block model of intervention. As little as 15 minutes of home program practice four times per week over an eight week block of therapy was shown to be effective in improving functional goals and quality of upper limb skills (Quality of Upper Extremity Skills Test) [26]. It remains unclear whether a more intensive model of upper limb training is superior to a distributed standard care model augmented by a functionally focused home program to achieve a similar dosage of therapy to improve upper limb unimanual, bimanual and individualized outcomes.

This current study proposes a hybrid model which will sequentially combine modified constraint induced movement therapy (mCIMT) followed by intensive bimanual training (called COMBiT) and compare this to a standard upper limb training model in a randomised trial. We propose to compare the intensive group based COMBIT model (one week of 30 hours of mCIMT followed by one week of 30 hours of bimanual training of which 45 hours was direct and 10 hours of indirect upper limb training) to standard care delivered in an individualised and distributed model (standard occupational therapy (OT); total dose 45 hours direct and indirect over 12 weeks) for improving outcomes as they pertain to activity and participation for children with congenital hemiplegia. Standard care for children with congenital hemiplegia will be six weekly sessions of 1.5 hours of OT provided in an individualised format (9 hours direct) in combination with an individually designed home program delivered over a 12 week period (36 hours indirect training). Each approach, COMBiT or standard care may follow intramuscular BoNT-A injections to the forearm provided as part of standard clinical practice that is delivered to reduce forearm spasticity prior to upper limb training.

We intend to determine if COMBiT is effective in providing a superior and lasting benefit, compared to standard therapy. As therapy programs are resource intensive and time consuming it is important to determine if an intensive program such as COMBiT is superior to standard distributed models of conventional therapy for improved and sustained outcomes. If the effects of COMBiT are sustained and superior over a six month period this could offer a cost effective, timely model of care. This study has been funded by the National Health and Medical Research Council (NHMRC) of Australia (Project Grant 1003887).

## Methods and analyses

A matched pairs randomised comparison trial will be conducted to evaluate whether a novel rehabilitation model (COMBiT) will be more effective than conventional standard care (OT) for improving upper limb function in children with congenital hemiplegia.

The primary hypothesis to be tested is:

H^1^ COMBiT will reduce activity limitations (improve unimanual capacity and bimanual performance) to a greater extent than standard care.

The secondary hypotheses are:

H^2^ Use dependent neuroplasticity and neurovascular changes (fMRI) will be more extensive and retained for a longer duration in children undertaking COMBiT than those engaged in standard care.

H^3^ COMBiT will be more effective compared with standard care to increase participation and enhance quality of life.

Two broad aims will be addressed:

The primary aim of our study is to determine which model of upper limb training leads to greater changes in upper limb activity performance and whether changes are maintained to six months post intervention.

A secondary aim is to further our understanding of the central neurovascular mechanisms underlying changes in upper limb function according to the type of training applied. Improving our understanding of the mechanisms underpinning treatment efficacy is an essential next step towards providing effective treatment and sustained outcomes. In addition, understanding the nature and timing of the brain lesion and relationship to treatment response may assist with effective allocation of resources.

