### Sample size

The primary basis for sample size calculation for this study is adequate power for the primary hypothesis: H^1^ comparison between the functional effects of COMBiT compared to standard care at 26 weeks. Based on data from the previous study [25] a mean difference of 7 units (10% of the control group mean at baseline on the Melbourne Assessment of Unilateral Upper Limb Function (MUUL) is proposed as the minimum difference likely to have clinical implications [27,28]. We assume a standard deviation of 9 units. Based on a comparison with alpha = 0.05 and 80% power, 25 subjects in each group (n=50) are required.

For H^2^, our previous upper limb has shown 90% success on 3 repeated fMRI scans [25]. Using 3T fMRI we can see activation in the representative cortex for motor studies with good signal to noise ratio. We allow for some loss of information due to subject refusal (10%) and scans where motion is a confounder (10%). With 40 participants in an analysis of baseline to week 13 changes on fMRI, this study will have 80% power to detect a difference between groups of 0.9 SDs. If we consider the supplementary motor area (SMA) given coefficients of variation (COV) for control subjects performing motor tasks (COV of 11% in PM1 and 35% in SMA) [29] and activation signal of 1.5%, we are able to detect differences in percentage activation levels over time as small as 0.47.

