COMBiT will be conducted over two weeks of the school holidays in a “day camp model”. Participants will attend a community facility “Flipside Circus” for six hours a day, five days a week from 9am to 3pm. In total, 45 hours of the day camp program will directly target upper limb training, and 10 hours will provide indirect use of the UL in more general gross motor upper limb activities. For both mCIMT and BIM training, the content will include intensive activity based practice, circus activities as well as self-care and recreational activities. The group will be led and supervised closely by five to seven therapy staff to achieve a ratio of one trainer to two children. Five core occupational therapists and one physiotherapist will plan and lead all intervention groups. Daily grading of activities and modification of tasks for the participants in each group will be performed by the core therapists. Tasks and activities will focus on reducing upper limb activity limitations identified at baseline assessment and target three occupational performance goals identified by the parents and/or child. Planning activities for each group will require task analysis, and develop guidelines for grading to challenge children with varying capabilities. Specific details of the content of the COMBiT weekly program contents are presented in Additional file 1: Table S1. Prior to commencement of the daily program, staff will be briefed and given specific tasks with written instructions outlining how each activity will be performed for the specific children they are supervising. Professional circus trainers will lead the two hour circus workshops. The core therapy team will meet with the circus trainers to design these programs and at the end of each session to discuss and modify the program as required and provide guidance to grading of tasks for participants. A debriefing session for the entire COMBiT group with staff members and separately for the staff and volunteers will be conducted at the conclusion of each day. The core therapy team will also meet daily to review individual participants’ goals and continually grade their program. A daily record of attendance will be kept and anecdotal information from the day will also be recorded.

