#### ***(ii) Standard care upper limb rehabilitation***

Standard care comprises an individualised and distributed model of occupational therapy upper limb training which consists of six sessions of 1.5 hours of individual direct therapy provided in a hospital or community setting over six weeks in combination with a 12 week home program. The weekly 1.5 hour sessions comprise one hour of direct therapy, and half an hour for home program development, demonstration and training with a total dose of nine hours of direct therapy. Families will be provided with a home program to practice goal areas for 12 weeks from the commencement of individual therapy sessions (30 minutes daily practice for six days/week for 12 weeks) for a total dose 36 hours of indirect UL therapy for the standard care group. The total anticipated therapy dose for standard care including direct therapy and home program practice is 45 hours of training.

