### Concurrent therapies

During the study children will not be provided with any additional concomitant upper limb treatments, such as arm splinting, casting or additional upper limb training. Children will return to their regular therapy programs at the completion of the 13 week follow up assessments. Documentation of concurrent therapy programs (ongoing, additional therapy or interventions, change in spasticity medications or lower limb interventions) will be recorded at each follow up assessment as these would not be able to be controlled over a six month period.

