## Statistical analyses

Analysis will follow standard principles for RCTs, using two-group comparisons on all participants on an intention-to-treat basis. Primary analyses will include all evaluable data. Sensitivity analyses will use imputation techniques to account for potential bias as a consequence of non-ignorable missing data during follow-up. The primary comparison H^1^ at 6 months will be based on the AHA and MUUL scores and will be between treatment groups using generalized linear models, with terms included to account for matching and, potentially, confounding variables such as baseline unimanual capacity. Secondary analyses will use similar methods to compare the outcomes between groups for participation (domains of LIFE-H) and QOL (domains of CP-QOL). Where continuous data exhibit skewness not overcome by transformation, non-parametric methods (e.g. Mann–Whitney U Test) will be used for simple comparisons.

For H^2^: The magnitude of central neurovascular changes between groups will be determined using quantitative analysis of fMRI statistical parametric maps will be performed using *iBrain*™: regions of interest will be delineated for each individual (primary motor cortex PM1, supplementary motor area (SMA), and ipsilateral motor cortex (PM1ipsi) and active voxels in those regions will be counted. These data will be compared for each region over time using generalised estimating equations approach. In subjects where mirror movements did not occur, lateralisation between ipsilateral and contralateral PM1 will be assessed using an objective approach^CIC#188^ to determine the incidence and magnitude of brain reorganisation. Statistical significance will be at p<0.05.

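### Visits are timed from the start of treatment, so maintenance at six months after treatment is measured in neither arm and retention cannot be compared between arms

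*Protocol article*

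**What the plan says.** The primary aim (Methods and analyses) is to find which model gives the greater change in upper limb activity and "whether changes are maintained to six months post intervention". H2 in the same section expects brain changes that "will be more extensive and retained for a longer duration in children undertaking COMBiT than those engaged in standard care".

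The abstract gives the schedule: "Outcomes will be assessed at 13 weeks after commencement, and retention of effects tested at 26 weeks". Sample size powers H1 as a "comparison between the functional effects of COMBiT compared to standard care at 26 weeks", and Statistical analyses says "The primary comparison H^1^ at 6 months will be based on the AHA and MUUL scores".

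The two treatments differ in length. Section (i) states "COMBiT will be conducted over two weeks of the school holidays". For standard care, section (ii) states "Families will be provided with a home program to practice goal areas for 12 weeks from the commencement of individual therapy sessions".

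Concurrent therapies first rules out additional upper limb treatment for the duration of the study. It then says "Children will return to their regular therapy programs at the completion of the 13 week follow up assessments". Later therapy is to be recorded at each follow-up, because it cannot be controlled over six months.

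**The concern.** An aim worded as maintenance after the intervention needs a clock that starts when treatment stops. The stated clock starts when treatment starts, and the two treatments stop ten weeks apart. At each visit the arms have therefore been off study treatment for very different times, and one of them by far less than six months.

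At stake is the durability claim. The Background presents COMBiT as a possible source of lasting benefit and of a cost-effective model if its effects persist. A statement that one arm held its gains better than the other would mix three things: true durability, time since treatment, and whatever therapy children received after week 13.

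**Working it through.** **Inputs**
- Visits: 13 and 26 weeks, from commencement (Abstract).
- COMBiT: 2 weeks (Study interventions; section (i)).
- Standard care: 12 weeks from the first session (section (ii)).
- Six months is taken as 26 weeks. The protocol treats them as the same point: Sample size uses one for H1 and Statistical analyses the other.

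**Step 1. Is the home program treatment or follow-up?** The plan's own dose reproduces: 6 sessions × 1.5 h = 9 h; 0.5 h × 6 days × 12 weeks = 36 h; 9 + 36 = 45 h. The home program is 36/45 = 80% of the standard care dose, and the claim of equal dose depends on it. Standard care therefore ends at week 12.

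**Step 2. Time since end of treatment = visit week − treatment duration.**

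| Visit | COMBiT | Standard care | Difference |
|---|---|---|---|
| Week 13 | 13 − 2 = 11 | 13 − 12 = 1 | 10 weeks |
| Week 26 | 26 − 2 = 24 | 26 − 12 = 14 | 10 weeks |

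In months, 24 × 12/52 = 5.5 and 14 × 12/52 = 3.2.

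**Step 3. Where would the visit named in the aim fall?** COMBiT: 2 + 26 = week 28. Standard care: 12 + 26 = week 38. The last stated visit is week 26, so the shortfall is 28 − 26 = 2 weeks and 38 − 26 = 12 weeks.

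**Step 4. Do other readings of the clock rescue the aim?**
- Clock from baseline, with the full permitted start delay of one month (taken as 4 weeks, an assumption): 26 − 2 − 4 = 20 weeks for COMBiT and 26 − 12 − 4 = 10 for standard care.
- Only the six weeks of sessions counted as standard care: 26 − 6 = 20 weeks.

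Neither reaches 26 weeks in either arm.

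**Step 5. Share of the interval in which regular therapy may run (weeks 13 to 26).**
- Of the 26 weeks from commencement: 13/26 = 50%.
- Of the time since COMBiT ended: 13/24 = 54%.
- Of the time since standard care ended: 13/14 = 93%.

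**Step 6. What this does to a retention comparison.** Suppose both treatments gave equal gains that faded at the same rate, fastest soon after stopping. COMBiT's early fading would fall before week 13 and standard care's after it. The change from week 13 to week 26 would then favour COMBiT with no difference in durability. At each single visit the same mechanism would work against COMBiT. This gives direction only; the protocol states no rate of decay.

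**The case against.** The strongest reply is that H1 is sound. Assessing both arms at the same time from start is the normal intention-to-treat comparison of a short block with a distributed program, and slower delivery is part of the strategy being compared. This stands. A reader might infer from the unequal intervals that the primary comparison is biased; the documents do not support that. If gains fade, the imbalance works against COMBiT at week 26, so it would not manufacture support for H1.

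Other parts of the reply also stand:
- Statistical analyses names no between-arm contrast of 13-to-26-week change in AHA or MUUL. The exposure lies in the wording of the aim, in H2, and in the planned comparison of fMRI regions over time. Even for H2, the power statement uses change from baseline to week 13.
- Later therapy is acknowledged and recorded, and the return to it applies to both arms. It would be wrong to say that it goes unmeasured.
- The two statements on concurrent therapy can be read as a bar up to the 13-week assessment and permission afterwards. The text does not put that limit on the bar, so it still needs reconciling.
- COMBiT at 24 weeks is close to six months; the large gap is in standard care.
- The abstract attaches commencement explicitly only to the 13-week visit, and Figure 1 is not shown. One clock for both visits is the natural reading, and no later visit appears in the text.

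What the reply does not remove is the conflict between the stated aim and the stated schedule. This is not detail left to a fuller document.

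**Conclusion.** The point holds as a mismatch between the aim and the schedule, and as a limit on what may be said about retention. The last visit is about 24 weeks after COMBiT and 14 weeks after standard care, against the 26 the aim implies. Between-arm statements about retention are confounded by a constant 10-week difference in time since treatment and by regular therapy after week 13. The randomised H1 contrast at 26 weeks remains valid as a comparison of strategies.

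This rests on both visits running from commencement and on the home program counting as treatment. The alternative readings checked change the intervals but do not reach six months after treatment.

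A reader might want a figure for the distortion in MUUL units. The documents cannot supply one. They give no decay rate, and the 7 units in Sample size are a difference between groups, not a gain within an arm. The Background also cites some effects that lasted six or 12 months after related therapies, so rapid fading cannot be presumed.

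**What to change.** Keep the visits and the sample size, and make these changes:

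1. State that 13 and 26 weeks both run from commencement.
2. Restate the primary aim as a comparison of the two strategies at 26 weeks from commencement, including any regular therapy after week 13, and replace the reference to six months after the intervention.
3. State that between-arm differences in 13-to-26-week change, clinical or fMRI, will not be interpreted as differences in retention, and limit H2 accordingly.
4. Report by arm the therapy already being recorded for weeks 13 to 26.
5. Reconcile the two statements under Concurrent therapies.

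A tempting repair is to compare COMBiT at week 13 with standard care at week 26 (11 and 14 weeks after treatment). I would not add it. It gives up the concurrent randomised comparison and sets a first follow-up test against a second. It also compares children who have not yet returned to regular therapy with children who may have had 13 weeks of it.

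The cost is wording and one table. The real price is a more modest claim about lasting benefit.
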